### Procedure

On the day of the induction attempt, having confirmed that women meet the selection criteria, they will be randomly allocated to one of three groups:**Dinoprostone group:** women assigned to this group will have a controlled-release non-biodegradable polymer vaginal insert containing 10 mg of dinoprostone (Propess® FERRING Laboratories-Switzerland) inserted, and the insert will be left in the patient’s vagina for a maximum of 24 h.**Vaginal misoprostol group (Misoprostol**_**v**_**):** women in this group will receive 25 μg of misoprostol (Misofar® BIAL laboratories, Spain) vaginally every 4 h for a maximum of 24 h (i.e., up to a maximum dose of 150 μg).**Oral misoprostol group (Misoprostol**_**o**_**):** women in this group will be treated using a dose escalation design described in detail in Fig. 1 of this protocol. In brief, they will follow what we call a 3 + 1 regimen, corresponding to a 3-h period on the drug followed by 1 h off the drug (3 doses, one per hour + 1 h of rest).

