### Blinding

Given the characteristics of the intervention, we will not attempt to blind patients or clinicians.

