### Sample size calculation

Taking data in the scientific literature on the rate of vaginal delivery within 24 h after the administration of the study drugs (70% for oral misoprostol [12], 55% for dinoprostone [12] and 54% of vaginal misoprostol [24]) as a reference, we will need to analyse 333 women (111 per arm) to detect significant differences between the groups with a power of 90% and a confidence level of 95%. Assuming a 10% rate of losses during the follow-up period, we will therefore need to recruit a total of 372 women (124 per arm).

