### Variables

The data collected will be recorded on case report forms, safeguarding patient confidentiality at all times. The primary outcome will be the rate of vaginal delivery (normal or instrumental) within the first 24 h after drug administration.

The secondary outcomes include cervical status (Bishop score of 6 or over, assessed 12 and 24 h after drug administration), percentage of caesarean sections, use of oxytocin and, if so, the total dose, duration of latent and active phases and the pushing stage of labour, induction failure (no progress into the active phase of labour after administering oxytocin for 12 ± 3 h after membrane rupture), uterine tachysystole, hypertonicity, hyperstimulation, or rupture, adverse events including maternal and/or foetal death, pain (assessed on a visual analogue scale), women’s satisfaction with the induction process (assessed using a dichotomous question, asked 2 days after childbirth or on hospital discharge), maternal morbidity (uterine rupture, severe postpartum haemorrhage or intensive care unit admission) and foetal morbidity (1- and 5-min APGAR scores, umbilical cord pH, and neonatal asphyxia, among other variables).

Due to the extensive information about misoprostol and dinoprostone in the literature, it was considered that a data monitoring committee was not needed. We report to the ethics committees yearly on the progress of the trial. Currently, we have no plans to make any major modifications to the protocol, but we will communicate any such modifications to all people involved.

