### Statistical analysis

First, we will describe the general characteristics of the sample. For this, percentages with 95% confidence intervals will be calculated for qualitative data and means and standard deviations for quantitative data.

Second, logistic regression analysis will be used to assess the relationship between the intervention received and the primary outcome (vaginal delivery within the first 24 h after administration of the corresponding drug). Crude and adjusted models will be constructed using variables found to be confounding factors in the univariate analysis.

Logistic regression analysis will also be used to analyse the rates of vaginal deliveries at 12 and 48 h after starting induction and the ripening of the cervix at 12 and 24 h. The rates of maternal adverse events (gastrointestinal adverse effects, uterine tachysystole, uterine rupture, uterine hyperstimulation, morbidity, postpartum haemorrhage, and fever) and of caesarean sections will be compared between the groups with a chi-square test.

Third, multiple linear regression analysis will be performed to explore the relationships between duration of the labour (total, and of active and latent phases), the maximum level of pain reported by the woman, 1- and 5-min APGAR scores, umbilical cord pH, and the intervention (vaginal dinoprostone, and oral or vaginal misoprostol). As well as crude models, adjusted models will be built controlling for intervention group. Complications and adverse events including neonatal asphyxia, morbidity, neonatal intensive care unit admission, and mortality and other complications will be compared between groups with a chi-square test.

Both intention-to-treat and per-protocol analysis will be performed. For the intention-to-treat analysis, we will consider all women included in the study who received at least one dose of any medicine. To handle any missing data on satisfaction, we will use multiple imputation techniques, taking into account age, parity and other potentially relevant variables. We will use the IBM SPSS Statistics for Windows, version 22.0, considering a *p* value of < 0.05 to be significant.

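### The set called intention-to-treat omits randomised women who were never dosed, and the primary model's wording does not guarantee analysis by assigned arm

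*Protocol article*

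**What the plan says.** All of the following is in the protocol article.

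- **Analysis sets (Statistical analysis).** Two sets are promised: "Both intention-to-treat and per-protocol analysis will be performed". The first is then defined: "For the intention-to-treat analysis, we will consider all women included in the study who received at least one dose of any medicine". Neither is named as the main analysis.
- **Primary model (Statistical analysis).** The exposure is described in these words: "logistic regression analysis will be used to assess the relationship between the intervention received and the primary outcome". No sentence says that women are analysed in the arm to which they were randomised.
- **Primary outcome (Variables).** It is the "rate of vaginal delivery (normal or instrumental) within the first 24 h after drug administration", so time zero is dosing and not randomisation.
- **Blinding.** The section states that "we will not attempt to blind patients or clinicians".
- **Timing of randomisation (Procedure).** Women are allocated "On the day of the induction attempt, having confirmed that women meet the selection criteria".

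**The concern.** Intention-to-treat means that everyone randomised is analysed in the arm assigned. The plan departs from the first half of that definition and is unclear on the second.

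**Who is included.** Leaving out undosed women does little harm when the decision not to start cannot depend on the allocation. Here it can, because the woman and her clinician both know the arm. The arms differ visibly by route, and the Background describes the oral route as generally better tolerated. The authors also expect oral misoprostol to do well. Refusal or withdrawal between allocation and first dose could therefore differ between arms, and the comparison of dosed women would no longer be fully protected by randomisation.

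**How they are grouped.** A model on the treatment received, read literally, would count a woman given another arm's drug under that drug. The inclusion rule adds to the doubt: it admits women dosed with any medicine and does not say where a woman dosed with something other than her assigned drug is counted.

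At stake is whether the result labelled intention-to-treat is the randomised comparison that readers will take it to be.

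**Working it through.** **1. Set the statements side by side.**

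| Element | Intention-to-treat requires | The article states |
|---|---|---|
| Women included | All randomised | Only those given one or more doses |
| Grouping | Arm assigned | Primary model described by treatment received; groups in Procedure defined by allocation |
| Time zero | Defined for every randomised woman | Drug administration, so undefined for a woman never dosed |

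The first row is a definite departure. The second is a conflict within the document. The third means that undosed women cannot be put back into the analysis without an added rule.

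**2. Inputs for an illustration of size.**

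- Women per arm: 124 (Sample size calculation). This reproduces from the article's own inputs: 111 / 0.9 = 123.3, rounded up to 124, and 3 × 124 = 372.
- Success rate among dosed women in one arm: 70%, the article's planning rate for oral misoprostol.
- Number of undosed women, *k*: not in the documents. Assumed 2, 4 or 6 of 124 (about 2%, 3% and 5%).
- Success rate among undosed women, *r*: not in the documents. Taken at its extremes, 0 and 1.

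**3. Formula.**

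All-randomised rate = [0.70 × (124 − *k*) + *r* × *k*] / 124.

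| *k* | *r* = 0 | *r* = 1 | Shift from 70%, in points |
|---|---|---|---|
| 2 | 85.4 / 124 = 68.9% | 87.4 / 124 = 70.5% | −1.1 to +0.5 |
| 4 | 84.0 / 124 = 67.7% | 88.0 / 124 = 71.0% | −2.3 to +1.0 |
| 6 | 82.6 / 124 = 66.6% | 88.6 / 124 = 71.5% | −3.4 to +1.5 |

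**4. Reading.** The shift equals (*k* / 124) × (*r* − 0.70). Its sign depends only on whether undosed women do better or worse than dosed women. Women who go into labour before dosing may often deliver vaginally, while those who need an early caesarean do not. The difference between two arms moves by the difference of their shifts, so similar exclusions in arms with similar dosed-set rates would largely cancel. For scale, the planning difference between oral misoprostol and dinoprostone is 70 − 55 = 15 points.

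No arithmetic is offered for crossover, because the documents give neither a rate nor a route for it.

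**The case against.** **Few women are likely to be affected.** Consent comes before inclusion, and allocation is on the day of induction after eligibility is confirmed, so little time is left in which to drop out before dosing. This stands and limits the size, but it also means that keeping these women in costs almost nothing.

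**The restriction is disclosed.** It is stated directly after the analyses are named. That is so. The label is still wrong, and labels are what carry over into a results paper.

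**The treatment-received wording may be loose.** A reader might infer that the main comparison will be as-treated. The documents do not support that. The inclusion sentence fixes who is counted and not how they are grouped, Procedure defines the groups by allocation, and the same section promises an intention-to-treat analysis. Table 1 and Procedure lead to oxytocin when the study treatment ends or fails, and no passage sends a woman to another arm's study drug. What remains is an unresolved conflict of wording.

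**Bias towards the favoured arm.** A reader might infer that the exclusion favours oral misoprostol. That would require the undosed women to be mainly in that arm and mainly failures. The documents say neither.

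**Lost power.** A reader might also link the rule to the gap between 372 recruited and 333 analysed. The article attributes that gap to something else: "Assuming a 10% rate of losses during the follow-up period". It is a planning margin and not a consequence of the one-dose rule.

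**An article may leave detail to the full protocol.** This covers silence on finer points. It does not cover a population rule that the article states and mislabels.

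**Conclusion.** The point holds in a limited form. The set called intention-to-treat is a modified one, and in this unblinded trial the exclusion of undosed women can depend on the known allocation. The description of the primary model conflicts with the promised intention-to-treat analysis, so analysis by randomised arm is not guaranteed. It is not shown to be abandoned.

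The size is probably small and its direction unknown. With 2 to 6 undosed women in an arm of 124 and 70% success among the dosed, the all-randomised rate lies between about 67% and 71.5%. Those counts are assumptions, and the ends of the range assume that all the undosed women fail or all succeed. The plan should be corrected, but the weakness does not undermine the design.

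**What to change.** 1. Define intention-to-treat as all randomised women, analysed in the arm assigned, and name it the main analysis.
2. In the primary logistic model, replace *intervention received* with *assigned arm*.
3. For women never dosed, count the 24 h from randomisation.
4. Rename the one-dose set modified intention-to-treat, and report it together with the per-protocol set as sensitivity analyses.

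**Cost.** A few sentences, plus delivery time and mode for a small number of undosed women. Women are followed to discharge, so these should already be in the hospital record. There are two drawbacks: slight dilution of the treatment contrast, and a different time origin for the few undosed women. The modified intention-to-treat sensitivity analysis covers both, since it leaves those women out and keeps a single clock.

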### Ethical considerations

Before inclusion, women will be asked to give written informed consent by their gynaecologist. This study has been approved by the Clinical Research Ethics Committee of Araba University Hospital and the Spanish Agency of Medicines and Medical Devices.

## Discussion

Given that a growing percentage of women undergo induction of labour [4, 5], it is important to determine the best method for this process. There are reasons to assert that misoprostol is the best drug, since as well as being inexpensive, it can be stored at room temperature, and has high efficacy and a good safety profile, especially when administered orally [25, 26].

On the one hand, this study is one of the few that attempts to use titrated doses according to uterine response, which may result in a lower rate of hyperstimulation and caesarean sections compared to vaginal administration of misoprostol [25]. Further, despite the safety associated with the rapid clearance of oral misoprostol [27], in our trial, we will progressively increase the doses (by 10 μg) with 1 h of observation off the drug for every 3 h in which doses are given, thereby further increasing the levels of safety.

On the other hand, our formulation allows more accurate dosing than those used in other studies [12, 25, 28] In previous studies, the drug in solution has been obtained by dissolving a 200-μg tablet of misoprostol in 200 ml of water, and the solution has been kept for up to 24 h. A syringe has been used to obtain the volumes to be given the women from this solution, assuming that in 1 ml of solution there will be 1 μg of drug [12, 28] This approach does not, however, take into account the potential precipitation of the drug or that it may not be homogenously dissolved, and hence, may lead to dosing errors. In contrast, in our study, we will use 20 and 30 μg capsules, which will be dissolved in water just before administration.

If the hypothesis of this study is confirmed, oral misoprostol in titrated doses may come to be considered the most effective and safe option for pre-induction/induction of labour in women with unfavourable cervix.

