**Discussion:**

The proposed study seeks to gather evidence on which of these three therapeutic options achieves the highest rate of vaginal delivery with the best safety profile, to enable obstetricians to use the most effective and safe option for their patients.

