Since induction of labour is an increasingly widely used procedure, it is important to identify a pharmacological agent that is effective as well as safe. Given previous research findings, we expect in this open-label randomised clinical trial that the use of oral misoprostol may help improve the rate of vaginal labour while maintaining a good safety profile.

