## Methods/design

### Aim

The objective of this study is to assess which of the three options considered, vaginal dinoprostone or vaginal or oral misoprostol, achieves a higher rate of vaginal delivery within the first 24 h after drug administration in women who undergo elective induction of labour due to their pregnancy becoming prolonged.

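### The anticipated conclusion covers safety as well as effectiveness, but the planned chi-square tests of harms cannot support a safety conclusion at 111 women per arm

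*Protocol article*

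**What the plan says.** Three places in the protocol article bring safety into the anticipated message.

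- Abstract, Discussion: the study seeks evidence on "which of these three therapeutic options achieves the highest rate of vaginal delivery with the best safety profile".
- Background, last paragraph under Oral misoprostol: the investigators expect that oral misoprostol "may help improve the rate of vaginal labour while maintaining a good safety profile".
- Discussion, closing paragraph: if the hypothesis is confirmed, "oral misoprostol in titrated doses may come to be considered the most effective and safe option".

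The inferential parts of the plan are narrower.

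- Aim: to find which option "achieves a higher rate of vaginal delivery within the first 24 h after drug administration".
- Variables: "The primary outcome will be the rate of vaginal delivery (normal or instrumental) within the first 24 h after drug administration".
- Sample size calculation: 111 women analysed per arm, based only on delivery rates of 70%, 55% and 54%.

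Harms are secondary outcomes. The list in Variables includes "uterine tachysystole, hypertonicity, hyperstimulation, or rupture, adverse events including maternal and/or foetal death", together with caesarean section and maternal and foetal morbidity. Under Statistical analysis, the rates of maternal adverse events and "of caesarean sections will be compared between the groups with a chi-square test"; neonatal complications are handled in the same way. Apgar scores and umbilical cord pH are analysed by linear regression. The 95% confidence intervals mentioned there are for percentages that describe the sample, not for differences in harm between arms.

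**The concern.** A between-group chi-square test yields a p value. Across three arms it does not say which arm differs, and it never says how large a difference the data leave open. A conclusion that one option is safe, or has the best safety profile, needs both. If the harm tests come out non-significant, the article offers the reader nothing else on which to judge safety, and a null test at this size is weak evidence of similarity.

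This matters because the Background names excess uterine activity as the main adverse effect of prostaglandins and says that it depends on route and dose. Those are the features that differ between the two misoprostol arms. A recommendation that includes safety would therefore rest on comparisons too imprecise to carry it.

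**Working it through.** **Inputs.** From the article: 111 women analysed per arm (124 recruited), 1:1:1 allocation, significance at p < 0.05. Assumed: two-sided testing, pairwise comparisons without adjustment, and harm rates of 1% to 20%, because the article gives no expected harm rates for its own arms.

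**The plan's own figure.** The allowance for losses reproduces: 111/0.9 = 123.3, rounded up to 124 per arm and 3 × 124 = 372. The 111 itself does not reproduce at 90% power: standard two-sided 5% formulas give 217 per arm for 70% v 55% and 192 for 70% v 54%. That is a separate matter. Here 111 is taken as given, and it was in any case derived from delivery rates and not from any harm.

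**Power for a difference in harm.** With p̄ the mean of the two rates p₁ and p₂, power = Φ[(|p₁ − p₂| − 1.96·√(2p̄(1 − p̄)/n)) / √((p₁(1 − p₁) + p₂(1 − p₂))/n)].

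For 5% v 10% with n = 111:
- p̄ = 0.075, and √(2 × 0.075 × 0.925/111) = 0.03536
- √((0.0475 + 0.09)/111) = 0.03520
- (0.05 − 1.96 × 0.03536)/0.03520 = −0.548, so power is 29%

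The same formula for a doubling from other rates:

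| Lower rate | Doubled rate | Power, 111 per arm |
|---|---|---|
| 1% | 2% | 9% |
| 2% | 4% | 14% |
| 3% | 6% | 19% |
| 5% | 10% | 29% |
| 10% | 20% | 55% |
| 20% | 40% | 91% |

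With 124 per arm, power for 5% v 10% is 32% and for 10% v 20% is 60%. From a comparator rate of 5%, the other arm would have to reach about 16.7% for 80% power at 111 per arm.

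**Illustration from the article.** The Background quotes caesarean rates of 20% (dinoprostone) and 11% (misoprostol). For that contrast power is 46% with 111 per arm and 50% with 124.

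**Width of the interval when the observed rates are equal.**
- Wald half-width = 1.96·√(2p(1 − p)/n). At 5%: 1.96 × √(0.095/111) = 5.7 points.
- Newcombe half-width = √((p − L)² + (U − p)²), where L and U are the Wilson limits. At 5% these are 2.2% and 10.8%, giving 6.4 points.
- Newcombe half-widths at 1%, 10% and 20% are 4.2, 8.2 and 10.5 points.

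Two arms both observed at 5% would thus still be compatible with a difference of about 6 points, which is larger than the rate itself.

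**Zero events.** The Background cites a trial with no hyperstimulation. If an arm of 111 women here had none, the two-sided 95% upper limit would be 1 − 0.025^(1/111) = 3.3%.

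**The case against.** A reader might infer that the plan lets a win on delivery rate, plus non-significant harm tests, count as proof of safety, or that safety plays no part in the hypothesis. The article does not support either reading. The expectation in the Background explicitly includes a good safety profile. The closing sentence of the Discussion is hedged and is not an analysis rule. No section equates a non-significant test with safety. Harms are listed and compared, and Apgar scores and cord pH are analysed by regression, which gives effect estimates. These points stand.

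It is also fair to say that powering on efficacy with harms as secondary outcomes is ordinary practice, and that naming a key safety measure or a margin is often left to an analysis plan that is not shown here. The absence of such a margin is therefore not the point.

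The numerical case has limits too. The 20% v 11% caesarean contrast comes from a retrospective study of vaginal misoprostol and 12 h dinoprostone after premature rupture of membranes. This trial requires intact membranes, and the closing claim concerns oral misoprostol, so the contrast shows scale only. All other harm rates are assumed, and for a common event (20%) a doubling would be detected with about 91% power.

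What remains is a mismatch between two things that the article does state: a conclusion that includes safety, and a test for harms that cannot deliver one. If the hypothesis includes safety, the article does not say what result would confirm that part.

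**Conclusion.** The point holds as a mismatch between the anticipated conclusion and the planned harm analysis, not as a stated wrong decision rule. With 111 per arm, and assuming two-sided unadjusted pairwise tests, a true doubling of a harm with a base rate of 1% to 10% would be missed between 91% and 45% of the time (100% minus powers of 9% and 55%). Equal observed rates in that range leave open differences of about 4 to 8 points. The limitation is serious for uncommon harms and modest for common ones; how much of it is clinically important depends on thresholds that the article does not give. The primary efficacy analysis is unaffected. This is a cheap improvement that changes what the trial can properly say about safety.

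**What to change.** - **Statistical analysis:** beside the chi-square p value, report the risk difference with 95% confidence interval for oral misoprostol v dinoprostone and oral v vaginal misoprostol, for caesarean section and for uterine hyperstimulation (as already defined under Table 1). That is 2 outcomes × 2 comparisons = 4 intervals.
- **Abstract and closing Discussion:** limit the conclusion that follows from the primary outcome to effectiveness. Say that any statement on safety will rest on those intervals, including the largest increase in harm that they leave open, and not on a non-significant test.

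No extra participants, visits or procedures are needed. The cost is four intervals, some rewording and a less favourable headline.
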